## Abstract

**Background:**

South Africa currently has the greatest number of people with HIV globally. The country has not yet met its 95-95-95 goals, with different gaps in the HIV care cascade for women and men. This paper reports on a protocol to pilot test a couple-based intervention designed to improve women's antiretroviral therapy (ART) adherence and men's engagement in care in heterosexual couples living in the Vulindlela area of KwaZulu-Natal, South Africa. Study goals are two-fold: (1) assess the acceptability, feasibility, and fidelity of the experimental intervention, START Together, and (2) collect efficacy data on START Together for women's ART adherence, men's engagement in HIV care, and the couple's relationship functioning.

**Methods:**

Women (*N* = 20) who were not engaged with ART adherence (defined via self-reported ART difficulties, record of missed clinic visits, or viral non-suppression) are the target patients; male partners are not required to know or disclose their HIV status to be part of the study. Couples are randomized 1:1 to the experimental treatment (START Together) or treatment as usual (referrals to the local clinic to support ART adherence or any other HIV-related care). START Together is a 5-session intervention based in cognitive-behavioral couple therapy, which is a skill-based intervention focusing on communication and problem-solving skills, and Life Steps, a problem-solving intervention identifying barriers and solutions to medication adherence. Couples are assessed at baseline, post-treatment (8 weeks post-randomization), and follow-up (12 weeks post-randomization).

**Conclusion:**

This study will provide preliminary implementation and efficacy data on whether this novel approach has potential to improve women and men's HIV and healthcare-related needs.

## Introduction

1

The 95-95-95 goals were developed by UNAIDS to test, treat, and maintain antiretroviral therapy (ART) adherence for 86% of people with HIV [1]. Important changes in the HIV care landscape have propelled countries forward towards meeting these goals, including widespread rollout of HIV care for pregnant and postpartum women, improved ART regimens and their access, and a focus on key populations driving the epidemic, including the targeting of men [[2], [3], [4], [5]]. Yet in many places, including in South Africa, which has the greatest number of people with HIV, there are still significant gaps in achieving the 95-95-95 goals [5].

For women living with HIV in South Africa, 94% are aware of their status, 78% are on ART, and 72% are virally suppressed. For men, these numbers are lower at every stage of the cascade: although 91% are aware of their HIV-positive status, 53% are on ART, and only 43% are virally suppressed [5]. It is clear that despite widespread advances in HIV care, targeted and more intensive interventions are still needed to engage women and men throughout the HIV care cascade in order to reach the goals set out by UNAIDS to end the epidemic.

One promising intervention approach to improve HIV outcomes in South Africa and other similar settings is the use of couple-based interventions (CBIs), where both partners in a relationship (typically romantic relationship, though other dyads are possible) attend and participate in treatment together. Theoretical frameworks that underlie CBIs for HIV or other health issues generally assume that improved health occurs in part through improvements in the dyad's functioning [[6], [7], [8]]. Crepaz and colleagues (2015) showed in a meta-analysis that CBIs were more efficacious than individual-based interventions (where only one person participated) in improving a number of HIV-related outcomes [9]. Since then, several other CBIs have also shown promising results when addressing HIV testing [10], HIV risk reduction [11], and outcomes for pregnant women with HIV and their babies [12]. A CBI focused on improving ART adherence and engagement in care for non-pregnant women has not yet been tested [13].

One of the benefits of using a CBI is that it offers the possibility that both partners can receive benefit from the intervention, even if the treatment is not targeting both partners equally. For example, a CBI in South Africa that aimed to reduce men's risky drinking and HIV risk also had benefits for female partners who participated, through decreased HIV acquisition and improved communication with their partners [11,14]. Similarly in Kenya, a CBI delivered in the home to reduce HIV risk for pregnant women improved the couple's communication, as reported by both partners, which led to increased couple efficacy and uptake of more HIV prevention behaviors [15]. Engaging men in care, which has historically been very challenging [16], may be better addressed for some men through the use of a CBI, as there is evidence that men will engage in care to support their family or a female partner [17]. Framing the intervention as one to improve women's ART adherence may be a more palatable message for men, who otherwise would not participate or prioritize their own healthcare.

### Trial objectives

1.1

The goal of the current trial is to assess (1) feasibility, acceptability, and fidelity of delivering a CBI that is framed as improving women's ART adherence and (2) efficacy of the intervention on women's ART adherence, men's engagement in HIV care, and the couple's relationship functioning. This manuscript provides an overview of the protocol and is written in accordance with the Standard Protocol Items: Recommendations for Interventional Trials (SPIRIT) guidelines.

## Methods

2

### Trial design

2.1

The study uses a randomized controlled trial design with two arms: (1) the experimental intervention, START Together, and, (2) treatment as usual (TAU), which serves as the control group. Couples who are eligible for study participation are randomly assigned to either TAU or START Together at a ratio of 1:1. Randomization sequence is generated using the randomization module on REDCap, the web-based platform used for data entry [18]. The randomization sequence is not revealed until study staff click ‘randomize’ in REDCap.

### Participants and study procedures

2.2

#### Eligibility criteria

2.2.1

The inclusion criteria for couple eligibility for the study are the following: (1) aged 18 or over, (2) currently in a committed, heterosexual, monogamous romantic relationship for at least 6 months, based on self-report, (3) woman is living with HIV and diagnosed at least 3 months prior to study entry, (4) woman demonstrates difficulty with HIV treatment engagement in the past year, defined as either self-reported ART adherence difficulties, evidence of missed clinic visits collected from medical records, or evidence of not being virally suppressed, defined as ≥ 50 copies/mL based on local standards [19], (5) willing to participate in treatment to support the woman's ART adherence, (6) reside in Vulindlela, or neighboring community, defined as spending ≥4 nights per week in the community, (7) willing to have intervention sessions audio-recorded (if randomized to START Together), and (8) able to comfortably communicate in either isiZulu or English. We chose to enroll women who demonstrate any barriers to ART adherence (either via clinic records, self-report, or viral non-suppression) given the evidence that any barriers to care are associated with increased mortality in South African women [20]. Study exclusion criteria are either of the following: (1) report of moderate or severe relationship violence, as measured by endorsing any item on the 5-item physical violence or 3-item sexual violence subscales of the WHO Intimate Partner Violence Scale [21] or (2) either partner previously participated in a CBI for HIV prevention or treatment. Fig. 1 depicts the study's flow in a CONSORT diagram.

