Informed consent is completed by trained staff members. Additional consent is obtained to extract data from participants' medical charts. Once consented, each member of the couple completes their baseline assessment separately. Assessments are conducted by research assistants of the same gender as the participants, if possible. During the baseline assessment, the assessor asks participants about their willingness to participate in the study as an additional strategy to ensure participants are not being coerced into study participation. Furthermore, the baseline assessment is used to further verify that the couple is in a bona fide romantic relationship given our team's past experiences recruiting couples where non-couples have feigned being a relationship in order to enroll in the study [22]. To ascertain the couple is in a bona fide romantic relationship, we ask a few informational questions to each participant regarding the partner; responses are compared after the assessment is complete. Examples of these questions include location/area of where the partner was born, employment status, and educational attainment. Similar procedures have been used in the recruitment of couples for intervention studies at this location [10].

The baseline assessment includes a battery of measures that assess previous HIV infection and treatment history, domains pertinent to relationship functioning (e.g., trust, intimacy, sexual satisfaction), and healthcare utilization. All measures have undergone a translation and back-translation process from English into isiZulu. All women (and any men who report being HIV-positive) complete a dried blood spot test to determine viral load (one of the possible ART non-adherence eligibility criteria for women) if a recent (past 30 days) viral load test is unavailable in their medical records.

Couples who meet all eligibility and none of the exclusion criteria above are eligible for study participation and randomized to either TAU or START Together by study staff initiating the randomization function in REDCap. Post-randomization, couples complete the study interventions and assessments according to those in Table 1. For START Together couples, they must initiate the first treatment session within 12 weeks of randomization. We did not a priori set an upper limit on the length of time couples were required to complete the intervention sessions by, to allow for flexibility in this pilot study.

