#### Efficacy outcomes

2.5.2

***Women's ART adherence.*** The amount of HIV viral copies extracted from medical records (past 30 days) or dried blood spots is used as an indicator of adherence to ART. A viral load of <50 c/mL is considered virally suppressed according to South African guidelines [19]. This is supplemented with participants' self-report of adherence to ART using the 3-item Ira Wilson adherence measure [39], which has been previously used in South Africa [40,41]. Blood samples are stored in a secure area at the Human Sciences Research Council and are tested by a local laboratory service. Viral load is collected at baseline and 12-weeks and self-report ART adherence is collected at baseline, 8-weeks, and 12-weeks.

***Men's engagement in HIV care.*** Dichotomous engagement in care (yes/no) is extracted from men's clinical records (if available) and supplemented with self-report at 12-weeks. Appropriate engagement in care depends on men's HIV status and current level of engagement. For men who are HIV-negative, receiving an HIV-test after 3 months is appropriate engagement in care. For men who are living with HIV but are not taking ART, initiating ART is the next appropriate step in the HIV care cascade. For men living with HIV who take ART but are not virally suppressed, improving adherence and achieving viral suppression is the next level of care engagement. Regardless of men's initial level of care engagement, achieving the next milestone in the HIV care cascade is recorded as positive for engagement in care.

***Couple's relationship functioning.*** A 39-item self-report measure assessing factors of relationship functioning was developed based on qualitative work assessing local definitions of healthy relationships with men and women in committed relationships from Cape Town and Vulindlela communities [42,43]. The factors are active relationship building, open communication, and couple-level problem-solving.^1^ Preliminary quantitative data from this measure show adequate reliability of the constructs, with alpha values ranging from .69 to .81 [44]. Assessment occurs at baseline, 8-weeks, and 12-weeks.

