### Power, sample size, and data analysis

3.1

The primary efficacy outcome, for which a power analysis can be calculated, is women's viral suppression. Only one prior study examined the efficacy of a CBI for ART adherence with serodiscordant couples in the US and found that after a 4-session intervention, 47% of the intervention group compared to 25% of the control group (who received referrals to medical provider) had at least 90% adherence to their ART [45]. Based on this, a power analysis was conducted using G*Power 7 [46] comparing the proportion of the sample reaching viral suppression between the two treatment arms.^2^ Using a two-tailed test and equal allocation of the sample between the two treatment arms, to achieve a power of .80 would require a total *N* = 148 (*n* = 74 in each arm). Because the current study is a pilot trial focused on feasibility and acceptability of the proposed intervention and collecting preliminary efficacy data on the intervention, our sample size will be *N* = 20 couples (*n* = 10 couples in each arm). A sample size of 20 represents the smallest sample size deemed appropriate for any statistical modeling [47]. The study will therefore be underpowered to detect significant differences between study arms in the efficacy outcome. We will instead focus on the direction of effects.

Descriptive statistics will be reported for implementation outcomes. For feasibility and acceptability, the proportion of the sample meeting the definitions used to define these constructs (see Measures) will be reported. Means, standard deviations, and ranges will be reported for the self-report measures of feasibility and acceptability, as well as for fidelity. We will compare these descriptives to previous behavioral couple- and family-based interventions in sub-Saharan Africa [10,48].

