To analyze the efficacy outcomes, we will use an intent-to-treat analysis, where all individuals will be analyzed according to the condition to which they were randomized. Generalized linear mixed models (GLMM) will be used to compare the two treatment arms (START Together vs. TAU) over time on women's ART adherence, men's engagement in care, and couple's relationship functioning. GLMM increases power by including all available data points and is appropriate for continuous, dichotomous, and proportional variables [49]. We will compare the groups on relevant clinical and demographic factors (e.g., age) that exist between the two treatment arms. A priori, we do not plan to include clinical covariates in the analyses given the small sample size. Moreover, although we will not be able to statistically account for variability in session attendance in the START Together treatment arm (including whether or not booster sessions were attended), this information will be provided descriptively to aid in contextualizing the efficacy results.

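### Entry admits women already at the primary efficacy outcome, no baseline-suppression stratum is described, and chance imbalance at 10 per arm can distort the direction of effect the trial will read

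*Protocol article*

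**What the plan says.** **Entry.** Protocol article, section 2.2.1 (Eligibility criteria), asks for a sign, from the year before entry, that the woman has had trouble staying in treatment. The three accepted signs are: "defined as either self-reported ART adherence difficulties, evidence of missed clinic visits collected from medical records, or evidence of not being virally suppressed". One route is enough. The section says the breadth is intended: "We chose to enroll women who demonstrate any barriers to ART adherence (either via clinic records, self-report, or viral non-suppression"), and gives as its reason an association between barriers to care and mortality. Section 2.2.2 (Recruitment) confirms that viral load is only "one of the possible ART non-adherence eligibility criteria for women".

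**Baseline value.** Under section 2.2.2, women without a chart viral load from the past 30 days "complete a dried blood spot test to determine viral load" as part of the baseline assessment, which comes before randomization.

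**Outcome.** Section 3.1: "The primary efficacy outcome, for which a power analysis can be calculated, is women's viral suppression". Section 2.5.2 sets the threshold: "A viral load of <50 c/mL is considered virally suppressed according to South African guidelines". Viral load is measured at baseline and at 12 weeks.

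**Randomization.** Section 2.1 describes 1:1 allocation through the REDCap module and names no stratification factor.

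**Analysis and power.** Section 3.1 compares the arms over time with generalized linear mixed models (GLMM) that use all available data points, and adds: "A priori, we do not plan to include clinical covariates in the analyses given the small sample size". The power analysis, "comparing the proportion of the sample reaching viral suppression between the two treatment arms", takes 47% against 25% and arrives at 148 women. The trial itself enrolls 20 couples, is declared underpowered, and will look at the direction of effects.

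**The concern.** The same 50 copies/mL threshold defines one of the entry routes and the primary efficacy outcome, but the other two routes do not depend on it. The enrolled women are therefore likely to be a mix of two groups who answer different questions. Unsuppressed women can show whether the intervention helps to achieve suppression. Suppressed women can only show whether it helps to maintain it.

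With 10 women per arm and no stratum, the two groups can fall unevenly between the arms by chance. Baseline status is likely to predict 12-week status strongly, so an uneven split moves the result on its own. Low power is conceded in the article, but that does not dispose of the point. What the trial will read is direction, and direction is what such an imbalance disturbs.

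A second consequence concerns the published figure of 148. It makes no stated allowance for women who already have the outcome at entry, and a reader planning a larger trial with the same entry rule could take it at face value.

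**Working it through.** **Step 1. Reproduce the plan's figure.** Inputs from section 3.1: 47% and 25%, two-tailed, equal allocation, power 0.80. The significance level is not stated; 0.05 is assumed. The pooled two-proportion formula per arm, with mean rate p̄ = (0.47 + 0.25)/2 = 0.36, is

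n = [1.960·√(2·p̄·(1 − p̄)) + 0.842·√(0.47·0.53 + 0.25·0.75)]² / (0.47 − 0.25)²

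= [1.960·0.679 + 0.842·0.661]² / 0.0484 = 73.5, rounded up to 74 per arm, or 148 in total. The article's figure reproduces.

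**Step 2. Let a share s be suppressed at entry.** The documents do not give s, so a range is used. Assume that 47% against 25% applies only to unsuppressed women and that a proportion r of suppressed women stays suppressed in both arms. Then

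p(START Together) = (1 − s)·0.47 + s·r and p(TAU) = (1 − s)·0.25 + s·r.

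The difference is (1 − s)·22 points whatever r is. The same formula as in step 1 gives:

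| s | Difference | Total N, r = 100% | Total N, r = 90% | Power at N = 148 (r = 100% / 90%) |
|---|---|---|---|---|
| 0% | 22.0 points | 148 | 148 | 80% |
| 20% | 17.6 points | 252 | 250 | 57% / 57% |
| 30% | 15.4 points | 326 | 328 | 47% / 47% |
| 50% | 11.0 points | 564 | 604 | 30% / 28% |

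These values depend on equal retention. If the intervention also helps women to stay suppressed, say 90% against 75% (again an assumption), the differences at s = 30% and 50% are 19.9 and 18.5 points, and N is 196 and 220.

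**Step 3. Chance imbalance in the pilot.** With K of 20 women suppressed at entry and 10 allocated to each arm without strata, the number in one arm is hypergeometric(20, K, 10).

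| K | Arms differ by 2 or more women | By 4 or more |
|---|---|---|
| 4 | 58% | 9% |
| 6 | 63% | 14% |
| 10 | 66% | 18% |
| 12 | 65% | 17% |

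**Step 4. Effect on direction.** Trials of 10 per arm were simulated with a true 47% against 25% among unsuppressed women and equal retention. The table gives the share of trials in which the result favours TAU (ties not counted).

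| Suppressed at entry | Retention | Raw 12-week proportions | Change from baseline | Arms balanced on baseline suppression |
|---|---|---|---|---|
| 0% | – | 10% | 10% | 10% |
| 20% | 100% | 15% | 13% | 11% |
| 20% | 90% | 15% | 14% | 12% |
| 50% | 100% | 22% | 17% | 14% |
| 50% | 90% | 23% | 21% | 18% |

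Change from baseline is a simple stand-in for an arm-by-time contrast; it is not the GLMM itself. It removes part of the excess error, and balance removes more.

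**The case against.** **The analysis does not ignore baseline suppression.** A reader might infer from the sentence on covariates that it does. The documents do not support that: viral load is collected at baseline and 12 weeks, and the GLMM compares the arms over time, so baseline suppression is a repeated outcome in the model. What is not described is its use as a stratum, a covariate or a basis for separate reporting. For the same reason, an imbalance of 4 women should not be presented as a 40-point head start (4/10). That describes a raw 12-week comparison, which is not the stated analysis.

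**Suppressed women are not uninformative.** It is tempting to say that they cannot benefit. They cannot move from unsuppressed to suppressed, but they can lose suppression, and session 5 in Table 2 deals with relapse prevention and keeping gains. Their self-reported adherence can also improve. This stands, and it is a reason to report maintenance rather than to exclude these women.

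**The entry rule is a reasoned choice.** This also stands. Nothing here asks for narrower entry, and feasibility, acceptability and fidelity are untouched.

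**The figure of 148 decides nothing in this pilot, and its inputs are uncertain.** Both are true. The 47% and 25% are proportions with at least 90% adherence in a cited study. Whether that sample included people already adherent at entry cannot be seen, and the text of the footnote attached to the power analysis is not shown. It therefore cannot be said that 148 is wrong, only that the article states no allowance for suppressed entrants.

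**The gain is modest.** Most of the risk of a wrong direction comes from having 10 women per arm, which the article admits. That is fair: the gain is 3 points over change from baseline at 50% suppressed, and 1 to 2 points at 20%.

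**The article condenses a fuller protocol.** A stratum may be specified there. The point is therefore limited to what section 2.1 describes and to the combination of entry rule, outcome and power statement that the article does fix.

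**Conclusion.** The point holds in a limited form. Women already below 50 copies/mL can be randomized although suppression is the primary efficacy outcome. No stratum for baseline suppression is described, and the baseline value enters only as a GLMM time point. If half the women are suppressed at entry, balancing the arms on that status would cut wrong-direction results to 14% to 18%, from 22% to 23% on raw 12-week proportions or 17% to 21% on change from baseline. At 20% suppressed the gain is smaller: 11% to 12%, from 15% raw or 13% to 14% on change.

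N = 148 is arithmetically correct for 47% against 25% in the whole sample. If those rates hold only among unsuppressed women and retention is equal in both arms, about 250 to 600 would be needed with 20% to 50% suppressed at entry. Those figures rest on an assumed share and on equal retention; a maintenance benefit would bring N down substantially. Implementation outcomes are not affected.

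**What to change.** 1. Keep the broad entry criterion.
2. Stratify the REDCap randomization on baseline suppression (<50 against ≥50 copies/mL), or on entry route if the result is not back in time. If the full protocol already specifies this, say so in the article.
3. Beside the GLMM, report 12-week suppression separately for women unsuppressed at entry (achieving) and suppressed at entry (maintaining), with counts by arm.
4. State next to N = 148 that it assumes 47% against 25% in the whole sample and makes no stated allowance for women suppressed at entry. If a larger N is quoted, give it over a range of suppressed shares and name the retention assumption.

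**Cost.** Items 3 and 4 need no new data and remain possible if couples have already been randomized. Item 2 is a setting in the randomization module and uses a value already collected at baseline, but some couples admitted by self-report or missed visits may have to wait for the dried-blood-spot result. The subgroup cells will hold about five women per arm or fewer if the sample splits evenly, so they are descriptive only and carry no test.
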